### 2.5. Randomization

We will randomize patients into two groups using a cluster randomization method, where the patient population is stratified into two groups based on the locality (postal code) and a random 1:1 block allocation of postal codes (under the care of nursing teams) to either intervention or control group. The allocation of the groups will be concealed until participation is fully confirmed. 

The primary reason for cluster randomization is to limit treatment contamination between the intervention and control groups. As the nurses from home nursing services are allocated to the care of multiple patients within the same neighborhood (based on postal code), individual randomization may increase the risk of the control group learning about the nutritional intervention (type II error) from interactions with the assigned home care nurse.

We will engage a statistician who is not associated with recruitment to generate a random number list to determine the order in which the recruiting staff will visit the specified postal codes for participant recruitment. Postal codes with low residential density in Singapore (limited cluster size) may be excluded or combined with other postal codes if feasible. 

We aim to recruit 8 to 10 subjects per week and finish recruitment in 35 to 50 weeks. We determined this rate of recruitment as there are currently 500 to 600 individuals under home nursing care with known PI(s), with the expectation that 20% to 30% of individuals will not meet the selection criteria. For patients with multiple wounds, all the PI(s) in stages II and above will be included in the analysis.

### 2.6. Recruitment 

For each postal code, the trial statistician will develop a randomization schedule to determine the order of recruiters approaching participants for recruitment. This will ensure that all the postal codes are fairly represented in the recruitment phase. The recruiters will screen the eligibility of potential participants and approach them with verbal and written information to explain the study before seeking consent. Consent/assent procedures (e.g., by whom, how, and under what conditions will a subject have consented) are presented in the Supplementary Material. Due to the profile of the subjects and caregivers and the frequency of clinical visits, a 21-day window period will be implemented from consent to the baseline visit.

### 2.7. Blinding and Allocation Concealment

Subjects will not be blinded to group allocations due to the nature of this study, which is not a placebo-controlled trial but rather a real-world pragmatic study. Subjects, research dietitians, and nursing staff will be aware that they are in a study to examine the effects of nutritional intervention on pressure injury healing rates. The nursing personnel responsible for measuring wounds and gathering data will not be blinded, given their role in conducting follow-up with the participants as a component of clinical care. However, they will be randomized to ensure they do not attend to both the intervention and control groups. The research dietitians who are not part of the main study team will only have interaction with the intervention group participants, and they are blinded to the measurement of primary outcomes. The trial statistician will be blinded to the group allocation.

### 2.8. Training for Home Care Nurses and Research Dietitians and Treatment Fidelity

Before study recruitment, home care nurses will undergo training sessions by the Principal Investigator (Dietitian) on the topics of (A) *Nutritional Screening and Assessment* (3 h), (B) *Management of Malnutrition* (2 h), (C) *Nutritional Interventions for Pressure Injury* (3 h), and (D) *Study Protocol Familiarization* (2 h). This will be carried out in eight sessions over three months. The training will include formal teaching with education materials and self-learning modules/reading materials, with informal discussions post-training to engage with the nursing staff. This will ensure nursing staff understand the importance of individualized nutritional support for wound healing in addition to the usual nursing procedures. 

The research dietitians, research coordinators, and nurses will undergo group-specific training tailored to their role in the research to ensure consistent protocol implementation and data collection across all clusters. The research coordinators and nurses will be provided with standardized data collection forms and plans for dealing with fidelity issues about the interventions. Participants in both the intervention and control groups will receive identical information and instructions regarding the study, except for the actual intervention. The intervention group will be told they will receive extra nutritional support intervention and supplementation, while the control group will be told to receive the usual nutritional care based on the most recent recommendation from their usual healthcare provider.

### 2.9. Intervention

Based on the latest guidelines, the intervention group will receive an educational pamphlet on nutritional and wound care for participants/families, with an in-depth explanation by trained nursing staff and a research dietitian. The trained nurses will reinforce nutritional education (adequate energy protein/fluid intake and compliance to consumption of supplements) on visits without a dietitian. The nutritional intervention provided will be based on the “The European Pressure Ulcer Advisory Panel, the National Pressure Injury Advisory Panel, and the Pan Pacific Pressure Injury Alliance Prevention and Treatment of Pressure Ulcers/Injuries: 2019 Clinical Practice Guideline” [1,33].

A dietetic consultation at the baseline, day 30, and day 60 of the intervention will be performed by an experienced and trained research dietitian on optimizing nutritional intake to meet caloric/protein requirements, along with additional high protein high energy (HPHE) supplementation (commercial ONS) prescribed for participants who do not meet nutritional requirements (25–35 kcal/kg/d and 1.2–2.0 g protein/kg/d) [1,33]. The dietetic consultation will be performed via face-to-face home visits and/or teleconsultation (depending on participant and caregiver preference). Adjustments to the enteral feeding regimen will be made for patients who did not see a dietitian during their last hospital admission. 

A specialized nutritional supplement for wound healing (Arginaid, Nestle, Vevey, Switzerland) containing 4.5 g arginine, 156 mg Vitamin C, 40.9 mg alpha-tocopherol equivalents (Vitamin E), and 30 kcal will be administered twice a day via oral ingestion or tube feeding (mixed in 100 mL water) for 12 weeks (14 servings per week). Adherence to supplementation will be determined by recording the number of leftover products by participants or their caregivers, with confirmation of intake during the research dietitian or nurse visit on days 30, 60, and 90. 

### 2.10. Control 

The control group will receive an educational pamphlet on nutritional and wound care for patients/families based on the latest nursing and nutritional guidelines [1,33], with an in-depth explanation by trained nurses. The trained nurses will provide reinforcement of nutritional education during the planned visits as per usual practice over the 90 days. Standard care and follow-up, as per hospital care plans, with the home care nurse contacting the hospital dietitian-in-charge of the subject for verbal advice as per usual practice, will be followed. HPHE supplementation and dietary advice to meet nutritional requirements will be based on previous recommendations from the hospital dietitian-in-charge or clinician.

## 3. Outcome Measures

We included objective measures (area, wound healing rate, and proportion of participants with wound reductions) for the primary outcome measurements, as these measurable outcomes will be used for the economic evaluation component of this study. 

### 3.1. Primary Outcome Measurements 

Change in Pressure Injury Area from the Baseline: Measurement of the alteration in the surface area of the identified pressure injury (PI) at identified time points;Proportion of Participants with 40% or Greater Area Reduction: Calculation of the percentage of participants who exhibit a reduction in the PI area by at least 40% at the same time points.

For participants with multiple PIs, the most severe or largest same-stage PI will be selected for primary analyses. Data from additional PIs will contribute to secondary analyses. Assessments and treatment documentation will be conducted during scheduled home nursing visits. Both objective and patient-reported outcome measures are used for the secondary outcome measurements to ensure that crucial additional information is collected from the participant’s perspective. 

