### 2.4. Sample Size Estimation

The sample size calculation is based on the results reported by Cereda et al. [17], where an odds ratio (OR) of 2.0 for ≥ 40% improvement in wound area on patients receiving a specialized nutritional supplementation containing arginine is used. To have 80% power to detect this difference with a 2-tailed type I error of less than 5%, we require at least 144 subjects per arm. After assuming a 20% mortality and 10% withdrawal rate (based on a Cereda et al. [17] study of 16% mortality and 6% withdrawal and a Chaboyer et al. [22] study of 8% loss to follow-up), we plan to enroll a total of 380 subjects (190 per arm). As we will be undertaking an intention-to-treat (ITT) analysis, anticipated adherence will be one of the outcome measurements to determine if the intervention (education and supplementation) is acceptable to the participants (Supplementary Material Figure S1).

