### 5.5. Interim Analyses

We intend to conduct interim analyses for efficacy and futility when data are finalized for subsets of 100 and 200 subjects. Based on these interim findings, we might reassess our sample size to maintain the power required to detect a significant difference in the primary outcome between our two study groups. Sample size re-estimation may be performed to evaluate the power to detect a statistically significance difference in primary outcome between the intervention group and the control group based on an interim analysis. 

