## Figures and Tables

**Table 1 nutrients-16-00299-t001:** Exclusion criteria for the INCA Trial.

	Exclusion Criteria
1.	Septicaemia.
2.	Poorly controlled diabetes (*glycated hemoglobin level > 8.5%)* [20,26].
3.	Consumption of supplements will lead to fluid intake in excess of fluid restriction for the following conditions: Advanced renal disease not on dialysis (KDIGO [21,22] Stage G4 with an eGFR of 15–29 mL/min/1.73 m^2^ and Stage G5 with an eGFR of less than 15 mL/min/1.73 m^2^); Heart failure with reduced ejection fraction [27]; Advanced decompensated alcoholic and non-alcoholic liver cirrhosis [28,29].
4.	Current neoplastic disease or last chemotherapy or radiotherapy less than one year ago.
5.	Currently on immunosuppressive therapy.
6.	Palliative with *a lifespan of ≤ 3 months.*
7.	Known allergy reaction to L-arginine or phenylketonuria.
8.	Presence of an infected wound *(if it is the only pressure injury present on the participant).*
9.	Untreated diagnosed osteomyelitis [18,19,30,31,32].
10.	Pregnant women and children (there is limited evidence on the use of arginine in these groups).

**Table 2 nutrients-16-00299-t002:** Outcomes and the methods of measurement to be used in the cluster RCT.

Type	Outcome	Outcome Description	Measurement Method	Data Collection Time Point (t) and Time Frame	Performed by
Primary	Wound	Change in the area of pressure injury (cm^2^) from the baseline	Assessed by the change in wound area ^#^ from the baseline to the follow-up time points and measured with a 3D wound imaging device at the time of follow-up.	t_0_ baseline, t_1_ 30 days, t_1_ 60 days, t_3_ 90 days, t_4_ 6 months, and t_x_ 1 year Time frame: 1 year	Nurse
		The proportion of participants with ≥40% area reduction	Assessed by the number of participants with wound area ^#^ reduction ≥ 40% at the time of follow-up versus the baseline.	t_1_ 30 days, t_1_ 60 days, t_3_ 90 days, t_4_ 6 months, and t_x_ 1 year Time frame: 1 year	Nurse, CRC
Secondary	Wound	The proportion of participants with complete wound healing of the main wound	Assessed by the number of participants with complete healing of a wound ^#^, determined by clinical assessment and pressure injury staging.	t_1_ 30 days, t_1_ 60 days, t_3_ 90, t_4_ 6 months days, and t_x_ 1 year Time frame: 1 year	Nurse, CRC

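### Two primary outcomes at five visits with no primary visit or testing order: nothing in the article secures the 5% type I error for which section 2.4 sizes one test

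*Protocol article*

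**What the plan says.** Section 3.1 lists two primary outcomes. The first is change in wound area from baseline at time points it does not name. The second is "Calculation of the percentage of participants who exhibit a reduction in the PI area by at least 40% at the same time points". The abstract and section 1 name the same pair.

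Table 2 gives the visits for the binary outcome as "t_1_ 30 days, t_1_ 60 days, t_3_ 90 days, t_4_ 6 months, and t_x_ 1 year Time frame: 1 year". It gives the same five follow-ups, plus baseline, for area change. No visit is marked as the primary one.

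Section 2.4 rests on one comparison, an odds ratio of 2.0 for at least 40% improvement in area. The target is 80% power, and the result is stated as "2-tailed type I error of less than 5%, we require at least 144 subjects per arm". No calculation is given for area change.

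Section 5.1 assigns dichotomous outcomes to time-to-event analysis with a Cox hazard ratio, and continuous outcomes to between-group differences. Section 5.5 plans "interim analyses for efficacy and futility when data are finalized for subsets of 100 and 200 subjects" and adds: "Based on these interim findings, we might reassess our sample size to maintain the power required". It speaks of one primary outcome in the singular.

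Two passages do not match this list. Section 3 introduces the primary measures as "We included objective measures (area, wound healing rate, and proportion of participants with wound reductions) for the primary outcome measurements". Section 8.1 leaves out the 6-month visit that Tables 2 and 3 and section 10 include.

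**The concern.** The sample size belongs to one hypothesis tested once at 5%. The outcome sections describe a family of primary results, with nothing to say which one decides the trial, in what order they are tested, or whether one success is enough. If any of them could count as the primary result, the stated 5% would not apply to the claim that is finally made.

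The choice is also open to the data. An effect at day 30 that fades by one year, or an effect on area without one on the 40% criterion, could be presented as the primary finding or passed over. Which outcome and which visit are primary is protocol content, and this article states it, so an unseen analysis plan does not cover the gap. That plan may well hold the interim boundaries and the resizing method, so the concern over these is conditional.

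**Working it through.** **Inputs from the article.** Two primary outcomes (section 3.1); five follow-up visits each (Table 2); two-sided 5%, 80% power, odds ratio 2.0, 144 per arm, 380 in total (section 2.4); interims at 100 and 200 (section 5.5). **Assumed:** the correlations between test statistics and the control response rate, neither of which is given. Clustering is ignored throughout.

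**1. The plan's own figure.** With odds ratio 2.0, p2 = 2·p1/(1 + p1). The pooled formula is n = [1.96·√(2·p̄(1−p̄)) + 0.842·√(p1(1−p1) + p2(1−p2))]² / (p2 − p1)².
- At an assumed p1 = 0.41, p2 = 0.582 and n = (1.386 + 0.586)² / 0.1716² ≈ 132.1, so 133. With continuity correction it is 143.6, so 144.
- Without the correction, 144 is met at control rates of about 28-29% or 56%.
- 144 × 1.2 × 1.1 = 190.1, the planned 190 per arm.

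So 144 is attainable for **one** test at a full two-sided 5%.

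**2. Room for a second primary.** The smallest n per arm over all control rates (uncorrected formula) is 133 at alpha 0.05, 142 at 0.04, 153 at 0.03 and 161 at 0.025. An equal split between two outcomes needs 161-185 per arm for control rates of 25-60%. At 0.025, 144 per arm gives about 72-75% power for control rates of 33-55%.

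**3. Two outcomes, one visit, one look, each at 5%.** The error is 1 − P(|Z1| ≤ 1.96 and |Z2| ≤ 1.96).
- Independent: 1 − 0.95² = 9.75%.
- Correlation 0.5: 9.1%. Correlation 0.8: 7.8%.

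**4. Five visits, one look, each test at 5%.** Null test statistics were simulated as jointly normal, with correlation falling geometrically between visits. For six tests, the single Cox statistic was given the correlations that the binary outcome would have at day 90.

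| Adjacent visits / outcomes (assumed) | Six tests (5 area + 1 Cox) | Ten tests |
|---|---|---|
| 0.5 / 0.5 | 23.4% | 34.0% |
| 0.8 / 0.7 | 17.5% | 23.7% |
| 0.9 / 0.8 | 13.8% | 17.8% |

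That is about 14-24% for six tests and 18-34% for ten. Ten independent tests would give 1 − 0.95¹⁰ = 40.1%, an upper reference only.

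**5. Looks, one outcome at one visit.** Looks at 100, 200 and 380, each at 5%, give 11.2%. This applies only if no boundary exists. Resizing alone, with a single interim, N capped at 760 and an unadjusted final test, reaches about 5.8-6.2% at worst.

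**6. Check of the remedy.** Lan-DeMets O'Brien-Fleming bounds at information 100/380 = 0.263, 200/380 = 0.526 and 1 are z ≈ 3.82, 2.70 and 1.98. Simulation gives an overall error of 5.0%. Testing at 0.0475 instead of 0.05 raises the uncorrected n at p1 = 0.41 from 133 to 135 per arm.

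**The case against.** The strongest reply is that the article sets no per-test level and never says that any one result is enough. Alpha allocation, interim boundaries and resizing methods usually sit in the full protocol or analysis plan. This stands for the looks and the resizing. It also rules out saying that the trial fails to hold 5%; the article supports only that nothing in it secures the 5%.

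The reply does not reach the choice of primary outcome and visit. The article states these, and states them at odds with its own sample-size premise.

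A reader might infer more than the text supports on several points:
- **Ten primary tests.** Section 5.1 sends dichotomous outcomes to a Cox model, which could make the binary outcome one test over all visits. Ten is the upper reading and six the lower. If the visit list in section 8.1 were the right one, both counts would fall.
- **Stopping for efficacy, or resizing on the observed effect.** Section 5.5 writes no efficacy stopping rule and says only that resizing rests on interim findings. Resizing alone adds little (step 5).
- **A third primary outcome.** The healing rate in section 3 is one loose introductory phrase. The abstract, section 1, section 3.1 and Table 2 all list two.
- **Interims too late to be useful.** This is a feasibility question, not one of type I error, and section 5.5 does not say which visit the finalized data refer to. On day-90 data the first look is still usable. At 8-10 recruits per week and 90-125 days to the measurement, it falls when (100/8 + 90/7) × 8 ≈ 203 to (100/10 + 125/7) × 10 ≈ 279 of 380 are enrolled.

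**Conclusion.** The point holds in this form: two primary outcomes, each at five follow-up visits, have no primary visit, testing order or alpha split, while the sample size covers one test at 5%. Nothing in the article secures that 5%.

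If each test is run at 5% in one analysis, the chance of at least one false-positive primary result is:
- about 8-9% for two outcomes at one visit;
- about 14-24% for six tests;
- about 18-34% for ten tests.

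The ranges depend on assumed correlations of 0.5-0.9 between adjacent visits and 0.5-0.8 between outcomes, but every case lies above 5%. The roughly 11% for three looks on one test is conditional on no boundary in the analysis plan. At 144 per arm there is no room to share alpha equally between the two outcomes and keep 80% power.

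**What to change.** - **Sections 1 and 3.1, Table 2, abstract:** name reduction of at least 40% in the index wound at day 90 as the single primary outcome. It is the powered outcome, and day 90 is the end of the intervention. Test area change at day 90 next, at the same level, only if the first test succeeds. Make the other visits secondary.
- **Section 5.1:** state that this primary is analysed as a binary outcome at a fixed visit, with allowance for clustering, and that the time-to-event analysis is supportive. Otherwise the new primary would contradict the stated Cox analysis.
- **Sections 3 and 8.1:** bring the outcome wording and the visit list into line with section 3.1 and Table 2.
- **Section 5.5:** base any efficacy interim on that one outcome with alpha-spending bounds, for example Lan-DeMets O'Brien-Fleming with z about 3.82 / 2.70 / 1.98 at 100 / 200 / 380. If area change may also be tested at an interim, give it its own bounds. Base any resizing on blinded pooled data.

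An alpha split, or a rule that both outcomes must succeed at one visit, would also control the error. An equal split needs 161-185 per arm before attrition. Requiring both to succeed needs a power calculation for area change, which the article does not give.

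Cost: recruitment began in October 2023 (section 7), so this needs a protocol amendment before any unblinded look. The final test is at about 0.0475, and area change becomes the second test in the sequence. The sample size barely moves.

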### 3.2. Secondary Outcome Measurements

Proportion with Increased Severity in Pressure Injury Stages: The percentage of participants whose pressure injury progresses in severity (PI stage and area of wound);Proportion with Complete Pressure Injury Healing: The percentage of participants whose PIs fully heal;Proportion with Improvement in Health-Related Quality of Life (HRQOL): The percentage of participants showing enhancements in HRQOL, as measured by the standardized instrument EQ-5D-5L;Proportion with Nutritional Status Improvement: The percentage of participants with measured nutritional advancements;Change in HRQOL (EQ-5D-5L Utility Values and VAS): The measured alteration in HRQOL utilizing EQ-5D-5L utility values and Visual Analog Scale (VAS);Incidence of New PIs: The number of new PIs during the study period;Incidence of PI Wound Infections: The number of new infections in PI wounds during the study period;Mortality Rate: The death rate among participants during the study time frame;Unplanned Hospital Admissions and Length of Stay (LOS): The frequency and duration of unexpected hospital admissions within the participant group.

All the study data and outcome measurements listed in Table 2 will be recorded using the Research Electronic Data Capture (REDCap) system [34]. Sociodemographic data will be collected based on recommendations by a local systematic review of healthcare utilization in urban Singapore [35]. 

A window period of ±14 days will be implemented for all assessments and outcome measurements. If an outcome measurement is interrupted (e.g., malfunction of wound imaging equipment, secure cloud server downtime, or assessors unable to visit on the day of assessment due to participant’s request for postponement), the assessor will re-attempt the measurement within the window period. Any outcomes measured outside of this window period will be considered a protocol deviation. 

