### 2.3. Inclusion and Exclusion Criteria 

Patients will be considered eligible if they are able to provide written informed consent (patient or legal guardian). The patients can be on oral and/or enteral nutritional support. The exclusion criteria for the trial are presented in Table 1.

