### 5.1. Outcome Measures

Dichotomous Outcomes: The frequency of outcomes will be determined, and we will utilize time-to-event analyses. The hazard ratios (HRs) along with their 95% confidence intervals (CIs) will be determined using a stratified Cox proportional hazards model.Continuous Outcomes: The differences between the intervention and control groups, along with their 95% CIs and corresponding *p*-values, will be documented.

Both patient-level and cluster-level data will be analyzed. We will address any imbalances in individual data by adjusting statistically using a mixed-effects Cox regression model performed by a statistician blinded to the group allocation. 

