### 5.3. Subgroup Analyses

A planned subgroup analysis will be performed by targeting specific nutritional status and intake variables, route of intake (oral versus enteral), staging of PIs, gender, age group, compliance to intervention, and functional status. 

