		The proportion of participants with increased severity of pressure injury (PI stage)	Assessed by the number of participants with increased severity of wound ^#^ at follow-up. The severity of pressure injury is determined by the increase in pressure injury staging or the increase in the area of the wound if pressure injury staging remains the same at the follow-up time points.	t_1_ 30 days, t_1_ 60 days, t_3_ 90, t_4_ 6 months, and t_x_ 1 year Time frame: 1 year	Nurse, CRC
		The proportion of participants with a new wound infection	Assessed of the number of participants with new wound infection(s) at follow-up who are clinically diagnosed with confirmation from blood tests (e.g., C-Reactive Protein CRP, renal, and liver function tests).	t_1_ 30 days, t_1_ 60 days, t_3_ 90 days, t_4_ 6 months, and t_x_ 1 year Time frame: 90 days	Nurse
	Nutritional	Change in nutritional status	Assessed using the Global Leadership Initiative on Malnutrition (GLIM) criteria to determine the severity of malnutrition. Change in the nutritional status determined by the direction of the nutritional status shift from the baseline to follow-up.	t_1_ 30 days, t_1_ 60 days, t_3_ 90 days, and t_x_ 1 year Time frame: 1 year	Nurse, Dietitian
		Change in nutritional intake	Assessed by the change in average of energy, protein, and selected micronutrient intake derived from 3DFR. Three-day food records will be filled by the participants or caregivers at selected time points. If the family or participant is unable to fill out the record, photographs of meals can be taken by the subject or caregiver and sent to the CRC. Trained personnel will use food composition analysis software (DietPlan 7, Forestfield Software Ltd., UK) to determine the intake, adjusted to per unit kilogram weight of the participant The energy, protein, and micronutrient intake of the study subjects on enteral tube feeding will be determined by a calculation of the goal feeding regimen that the study subject has been prescribed prior to the start of the study.	t_0_ baseline, t_1_ 30 days, and t_1_ 60 days Time frame: 60 days	Dietitian, Nurse
	Quality of Life	Change in HRQOL	Assessed by the change in EQ5D-5L VAS and utility scores at follow-up from the baseline for the overall population and age categories, if appropriate, where changes in scores are expressed as mean differences or standardized mean differences.	t_0_ baseline, t_3_ 90 days, t_4_ 6 months, and t_x_ 1 year Time frame: 1 year	Dietitian, Nurse, CRC

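### Section 3.2 and Table 2 define the nutritional-status outcome differently; the section 3.2 percentage improved shuts out participants not malnourished at baseline and gives no weight to worsening

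*Protocol article*

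**What the plan says.** Section 3.2 names the outcome as "Proportion with Nutritional Status Improvement: The percentage of participants with measured nutritional advancements". That is a yes/no result for each participant.

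The corresponding row of Table 2 describes the measure as "Assessed using the Global Leadership Initiative on Malnutrition (GLIM) criteria to determine the severity of malnutrition" and adds "Change in the nutritional status determined by the direction of the nutritional status shift from the baseline to follow-up". That is a better / same / worse result. Table 2 places the follow-up assessments at 30, 60 and 90 days and 1 year, and Table 3 adds the baseline assessment.

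Neither section 2.3 nor Table 1 sets a nutritional-status criterion. On feeding, section 2.3 says only "The patients can be on oral and/or enteral nutritional support". Section 5 commits to analysing everyone randomized. For dichotomous outcomes section 5.1 states "The frequency of outcomes will be determined, and we will utilize time-to-event analyses", using a stratified Cox model. Nutritional status appears among the adjustment factors of the sensitivity analyses (section 5.2). Section 5.3 adds "A planned subgroup analysis will be performed by targeting specific nutritional status and intake variables".

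**The concern.** GLIM severity is an ordered grade. Reducing it to improved or not improved has two consequences that follow from the definition alone.

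- A participant already in the best grade cannot improve but still counts in the denominator. The highest attainable success rate is the share malnourished at baseline.
- A participant who becomes severely malnourished scores the same as one who stays put, so any decline that the intervention prevents is invisible.

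The protocol handles comparable outcomes more fully. Section 3.2 gives the wound both a healing and a worsening outcome, and gives quality of life both a percentage improved and a change in score. Nutritional status is close to what a nutritional intervention acts on, yet that section counts improvement only. Because Table 2 scores the same outcome another way, one dataset could give two different answers under one label.

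**Working it through.** **1. The two definitions side by side.** The document does not state the number of grades; three (none, moderate, severe) are assumed here.

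| Baseline to follow-up | Section 3.2 | Table 2 |
|---|---|---|
| severe to moderate | improved | better |
| severe to none | improved | better |
| none to none | not improved | same |
| none to severe | not improved | worse |
| moderate to severe | not improved | worse |

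The definitions disagree on every decline. Neither separates a one-grade from a two-grade shift.

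**2. The plan's own figure.** Section 2.4 powers only the wound outcome, "where an odds ratio (OR) of 2.0 for ≥ 40% improvement in wound area", with 80% power and a two-sided 5% test: 144 per arm. The control rate is not stated. Assume 0.40. The treated odds are 2 × 0.40/0.60 = 1.333, so the treated rate is 0.571. The two-proportion formula is

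n = [1.96·√(2·p̄(1−p̄)) + 0.84·√(p0(1−p0) + p1(1−p1))]² / (p1−p0)²

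With p̄ = 0.486 it gives 132.2, that is 133. The continuity correction, n/4 × [1 + √(1 + 4/(n(p1−p0)))]², gives 143.7, that is 144. The stated figure is therefore reproducible under an assumed control rate, but it was not set for nutritional status. It is borrowed below only as a plausible number per arm.

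**3. Assumed scenario for GLIM.** Control-arm follow-up probabilities (none / moderate / severe):

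- baseline none: 0.80 / 0.15 / 0.05
- baseline moderate: 0.20 / 0.60 / 0.20
- baseline severe: 0.08 / 0.27 / 0.65

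The intervention multiplies the odds of a better grade by 2.0 within each baseline grade. This raises improvement from 0.20 to 0.333 in the moderate group (odds 0.25 to 0.50) and from 0.35 to 0.519 in the severe group (odds 0.538 to 1.077). In the group not malnourished it cuts decline from 0.20 to 0.111 (odds of staying 4 to 8), and section 3.2 counts none of that benefit.

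**4. Percentage improved among all participants.** This is the moderate share × its rate plus the severe share × its rate. For a 20/40/40% baseline mix:

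- control: 0.40 × 0.20 + 0.40 × 0.35 = 0.220
- intervention: 0.40 × 0.333 + 0.40 × 0.519 = 0.341

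For a 60/25/15% mix the same sum gives 0.1025 and 0.161. The difference shrinks from 12 to 6 points although the treatment effect is unchanged.

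**5. Power at 144 per arm.** There were 1,000 simulated trials per row, with simulation error up to about 1.6 points (√(0.25/1000)). The tests were a two-proportion test on improved, a rank test on direction of shift, and a rank test on follow-up grade stratified by baseline grade, which stands in for a baseline-adjusted proportional-odds model.

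| Not malnourished at baseline (none/moderate/severe mix, %) | Improved | Direction | Ordinal grade | Loss, improved | Loss, direction |
|---|---|---|---|---|---|
| 5% (5/45/50) | 0.74 | 0.80 | 0.84 | 10 | 4 |
| 20% (20/40/40) | 0.65 | 0.73 | 0.82 | 17 | 9 |
| 40% (40/35/25) | 0.47 | 0.65 | 0.75 | 28 | 10 |
| 60% (60/25/15) | 0.34 | 0.63 | 0.70 | 36 | 7 |

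A second assumed model (correlated normal severity cut into three grades, 133 per arm from 190 × 0.70, odds ratios 1.75 and 2.0) pointed the same way. The ordinal analysis gained 17 to 45 points over improved and 4 to 21 over direction of shift. Neither model includes clustering or the Cox analysis of section 5.1.

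**The case against.** The strongest reply is that Table 2 is the detailed definition and section 3.2 a one-line entry; that this is one of many unpowered secondary outcomes; and that the model and denominator can be left to an analysis plan that is not shown. Much of this stands for the choice of model. It does not dispose of the outcome definition, which the article states twice and differently. An analysis plan faithful to section 3.2 would inherit the ceiling.

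Three stronger readings are tempting, and the documents do not support them.

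- *Both definitions ignore decline.* A direction of shift includes worsening, so Table 2 counts it.
- *Power falls sharply.* The documents give no baseline GLIM distribution, effect size or power for this outcome. The loss is modest if nearly everyone is malnourished and large only if a substantial share is not. The tests compared are also not the planned time-to-event analysis.
- *Baseline status is ignored, so imbalance between clusters will pass for a treatment effect.* Section 5.1 plans adjustment for imbalances in individual data, section 5.2 names nutritional status as an adjustment factor, and section 5.3 makes it a subgroup factor. What remains is that the outcome definition makes no use of baseline grade and that the named adjustment sits in the sensitivity analyses.

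**Conclusion.** The point holds in a limited form. Three things follow from the text without any assumption about the data: section 3.2 and Table 2 score a decline differently; the section 3.2 version caps success at the share malnourished at baseline and treats worsening as no change; and Table 2 discards the size of the shift. That the baseline will be mixed is an inference from the absence of an entry criterion and from the planned subgroup analysis; no figure is given.

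The cost in power is conditional. On the assumed three grades, odds ratio 2.0, 144 per arm and no clustering, the percentage improved loses about 10 to 36 points as the share not malnourished rises from 5% to 60%. Direction of shift loses about 4 to 10. These figures show how the choice behaves; they are not estimates of this trial's power. The outcome is secondary, so neither primary wound outcome is affected. The change is worth making because it is cheap.

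**What to change.** In section 3.2 and Table 2, give one definition: the ordinal GLIM grade at one named follow-up visit (for example day 90, the end of the intervention), with the grades listed. Analyse it with a proportional-odds model adjusted for baseline GLIM grade and accounting for clusters, and report the common odds ratio. Show the baseline-to-follow-up transition table by arm, with deaths reported alongside, since section 2.4 expects 20% mortality and those participants will have no later grade. Report the percentage improved only among those malnourished at baseline, with the percentage worsened beside it.

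The cost is wording; the GLIM assessments are already scheduled. The downside is that a common odds ratio is less familiar than a percentage and assumes proportional odds, which readers can check against the transition table.
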